### Sequence generation and randomization

Treatment allocation will progress in accordance with an electronically generated allocation sequence (https://www.sealedenvelope.com/simple-randomiser/v1/lists). The size of the allocation blocks (i.e., 3, 6, and 9) is randomized, and eligible participants will be stratified according to a present PTSD diagnosis to ensure that participants with PTSD are distributed equally across conditions. The allocation sequence will be stored with two independent staff members who perform the randomization, and is concealed from all researchers, therapists, and participants.

### Measures

#### *Demographics*

Data on demographic variables such as age, gender, and educational level will be collected for all participants.

#### Diagnostic measures

Diagnosis of nightmare disorder will be based on criteria for nightmare disorder in the DSM-5 [1]. To determine the presence of current comorbid Axis-I disorders, the Dutch Structured Clinical Interview for DSM-IV-TR Axis-I disorders (SCID-I; [54]) will be administered at pre- and post-assessment. The reliability of the Dutch SCID-I is good, with a mean inter-rater agreement of .71 (Cohen’s Kappa; [55]).

#### Treatment outcome measures

Treatment outcome measures will be assessed at baseline, post-assessment, and 3- and 6-month follow-up. For an overview of all assessments, see Table 1.

#### Primary outcome measures

The first primary outcome measure addresses *nightmare frequency.* There are two ways to measure nightmare frequency with the widely used Nightmare Frequency Questionnaire (NFQ; [56]). This instrument assesses (1) the number of nights with nightmares in the last week, and (2) the total number of nightmares in the last week. As most previous nightmare research is focused on the latter, rather than the former conceptualization of nightmare frequency (e.g., [11, 13]), the total number of nightmares in the last week constitutes the first primary outcome measure, while the number of nights with nightmares in the last week is considered a secondary outcome measure. Both variables are assessed by means of a one-question, self-report survey (see NFQ; [56]).

The second primary outcome measure addresses *distress caused by nightmares* and the impact of nightmares on everyday life as well as on sleep behavior, which is assessed with a 12-item measurement instrument constructed for this study. For this purpose, several items of the Nightmare Distress Questionnaire (NDQ; [57]) and the Nightmare Effect Survey (NES; [58]) were modified and served as a basis for the new survey. This newly developed Nightmare Distress and Impact Questionnaire (NDIQ) consists of two subscales. The first subscale addresses the impact caused by nightmares during the day (e.g., “Because of my nightmares, I cannot function properly during the day”), while the second subscale is focused on the distress caused by nightmares at night (e.g., “My nightmares disturb my sleep pattern”). Given that nightmares do not only cause sleep complaints, but also severe daytime suffering, the authors aimed at constructing a questionnaire that could clearly distinguish these two sources of nightmare distress. Items of the NDIQ are scored on a four-point scale: 0 (Not), 1 (A little bit), 2 (Somewhat), and 3 (Completely). Validation of this questionnaire is still ongoing. The sumscore of both subscales constitutes the second primary outcome measure, while possible effects of IR and IE on the two subscales will be explored separately.

#### Secondary outcome measures

The Zelf Inventarisatie Lijst (ZIL; [59]) will be used to measure *symptoms of posttraumatic stress disorder*. The ZIL is a 22-item Dutch self-report inventory covering the severity of PTSD symptoms in the last 4 weeks. In contrast to other measures of PTSD symptoms, the ZIL allows for the assessment of posttraumatic symptoms irrespective of the occurrence of a traumatic event. Given that the proposed study aims to include participants with posttraumatic as well as idiopathic nightmares, it is assumed that (at least) some participants will not have experienced a traumatic event. The ZIL, therefore, seems to be a suitable measure of PTSD symptom severity in the present sample. The reliability of the scale is good, with Cronbach’s *α* varying from 0.90 to 0.94 [60], and a test-retest reliability of 0.92 [61].

*Sleep complaints* will be assessed with the Dutch version of the Insomnia Severity Index (ISI; [62]). The English questionnaire is a valid and reliable measure to detect changes in insomnia severity (internal consistency = 0.78; [63]). Validation studies on the Dutch version of this questionnaire are not yet published.

*Dysfunctional beliefs* about nightmares will be measured with a newly developed Nightmare Beliefs Questionnaire (NBQ). The NBQ was constructed based on nightmare interviews with four pilot participants of the proposed study. Given that dysfunctional beliefs have been shown to play an important role in sleep disorders (e.g., [64]) as well as other psychological disorders (e.g., [36, 65, 66]), it seems worthwhile to construct a measure that can assesses such dysfunctional beliefs about nightmares. The NBQ is a 15-item self-report questionnaire that measures the degree to which patients hold certain beliefs about nightmares (e.g., “People who suffer from nightmares are weak” or “I cannot control my nightmares”). Items of the NBQ are scored on a four-point scale: 0 (Not), 1 (A little bit), 2 (Somewhat), and 3 (Completely). Outcome values consist of the sum of all items, which can range from 0 to 45. The principal investigators (AK and JL) created the NBQ for the purpose of the proposed trial. Validation of this questionnaire is still ongoing.

#### Other measures

To evaluate and monitor changes in the type of emotions involved in nightmares over the course of treatment, participants will be presented with a selection of emotions commonly associated with nightmares (i.e., anxiety, anger, sadness, shame, disgust, guilt, and helplessness). They are asked to select the emotions they experienced during their nightmare(s) and encouraged to write down any other emotions they might have experienced.

If participants experienced one or more nightmares during the previous week, they will be asked to fill out four questions about the impact of the nightmare(s). On four Visual Analog Scales (VAS) ranging from 0 (“not at all”) to 100 (“very much”), participants are asked to indicate the intensity of emotions during the nightmare(s), the vividness of the nightmare(s), how often they awoke from nightmare(s), and their sleep quality during the past week (ranging from “very bad” to “very good”). In addition, all participants are asked to indicate their average hours of sleep during the past week. Note that all measures reported here will be assessed weekly.

#### Mediators of change

In order to investigate temporal relationships between the mediators and outcome measures in a methodologically well-considered manner [20, 67], the weekly appointments and assessments will be separated by a minimum of 7 and a maximum of 14 days. Proposed mediators of change for the treatment effect of IR and IE are assessed 1 day after each treatment session (and after pre- and post-assessment). Participants are asked to fill out an online questionnaire about their nightmares in general. This questionnaire consists of seven VASs ranging from 0 (“not at all” or “very bad”) to 100 (“very much” or “very good”), which measure nightmare valence, predictability, controllability, and tolerability of emotions elicited by nightmares, mastery of the nightmare content, sleep quality, and nightmare distress. Between-session reductions in SUDs will be assessed by means of the imagery exercise described below (for an overview of the proposed mediators and their corresponding items, see Table 2).

**Table 2 Tab2:** Overview of proposed mediators

Mediator	Item
Predictability of emotions	“I think that I can predict the emotions elicited by my nightmares.”
Controllability of emotions	“I think that I can control the emotions elicited by my nightmares.”
Tolerability of emotions	“I think that I can tolerate the emotions elicited by my nightmares.”
Mastery of nightmare content	“I think that I am in control of the content of my nightmares.”
Nightmare valence	“When I think about my nightmares, I get emotional.”
Nightmare distress	“Nightmares have a negative influence on my daily functioning.”
Sleep quality	“How would you evaluate the quality of last night’s sleep?”
Reduction in SUDs	“How distressed do you feel right now?”

SUDs = Subjective Units of Distress

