One week after baseline assessment, participants will receive the first of three treatment sessions (separated by at least 7 days). In the beginning of each treatment session, participants will be asked to fill out the primary treatment outcome measures (for an overview of the assessments, see Table 1). One week after the last treatment session or after a 4-week waiting period, post-assessment will take place. In order to ensure objective assessment of the treatment effect, an independent assessor, who is blind to the participants’ condition, will conduct the assessment. Proposed mediators of the treatment effect will be assessed by means of online questionnaires, which are sent via automated emails 1 day after pre- and post-assessment and after each treatment session. For participants in the WL condition, the online mediator questionnaires are sent 1 day after pre- and post-assessment, and once weekly during the waiting period (separated by 7 days). All face-to-face assessments and therapy sessions will take place at the outpatient psychotherapeutic clinic (PsyPoli) of the Department of Clinical Psychology at the UvA.

**Table 1 Tab1:** Summary of measures

Measure	Description	T1	T2	T3	T4	T5	F1	F2
*Primary outcome measures*								
NFQ	Number of nightmares	+	+	+	+	+	+	+
NDIQ	Nightmare distress and impact	+	+	+	+	+	+	+
*Secondary outcome measures*								
NFQ	Nights with nightmares	+	+	+	+	+	+	+
ZIL	PTSD symptoms	+				+	+	+
ISI	Sleep complaints	+				+	+	+
NBQ	Nightmare beliefs	+				+	+	+
*Diagnostic measures*								
DSM-5	Nightmare disorder	+				+		
SCID-I	DSM-IV-TR Axis-I disorders	+				+		
*Mediators of change*		+	+	+	+	+		
*Imagery Exercise*		+	+	+	+	+		

*Note.* T1 = Pre assessment, T2 = Week 1, T3 = Week 2, T4 = Week 3, T5 = Post assessment, F1 = 3-month follow-up, F2 = 6-month follow-up. Mediators of change are assessed at T + 1 day. DSM-5 = *Diagnostic and Statistical Manual, 5th edition*; ISI = Insomnia Sensitivity Index; NBQ = Nightmare Beliefs Questionnaire; NDIQ = Nightmare Distress and Impact Questionnaire; NFQ = Nightmare Frequency Questionnaire; SCID-I = Structured Clinical Interview for DSM-IV-TR Axis-I disorders; ZIL = Zelf-Inventarisatie Lijst (Self-inventory List)

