#### Mediation

Mediators of the treatment effects for IR and IE will be analyzed according to the following steps: (1) mediator variables, which show a change during the course of treatment, will be included in the statistical model. For this purpose, the means across and within subjects over time will be inspected for all eight proposed mediators. In order to reduce the number of relevant mediator variables, we will inspect the association between the proposed mediators over time. A composite score will be calculated for those mediator variables that are highly associated with each other if their theoretical conceptualization allows for it. (2) In a series of separate mixed regression analyses, statistically relevant mediator variables will be selected from the remaining mediator variables. To that end, the effect of each mediator on treatment outcome will be explored regardless of treatment condition. Each mediator score (measured the day after pre-assessment and after all treatment sessions) will be used to predict treatment outcome at the following assessment (i.e., 6 days/nights later). (3) Only those mediator variables that have an effect on treatment outcome will subsequently be added to a final mixed regression model, taking treatment condition into account. Fixed factors in the model will, therefore, include: treatment condition (IE and IR), relevant mediators, time, and their interaction, as well as any relevant covariate that might reduce error. The covariance structure of the repeated part will be determined by empirically assessing the best fitting structure. If possible, random parts on the participant level will be added. Note that if a mediator represents a working mechanism, the strength of the association between mediator and effect (i.e., outcome) should be similar in all conditions [71]. Therefore, to investigate whether there is a difference between the working mechanisms of IR and IE, we will test whether the mean change for each mediator differs between treatment conditions (i.e., the larger the change, the more the treatment affects the mediator, indicating that the working mechanism is strongly triggered by the treatment). Also, we will inspect the percentage of variance of the clinical effect explained by each mediator, and whether treatments differ in the percentage of variance explained by a specific mediator. (4) In a last step, all previously determined relevant mediator variables will subsequently be tested with separate mediation analyses for IE and IR (with WL as a reference group). Difference scores of mediator assessments will be used to predict post-assessment outcomes. Pre-treatment levels of the dependent and mediator variables will be added to the model as covariates (see also [64]). Both single and multiple mediation analyses will be performed. Mediation will be tested by evaluating the 95 % confidence interval of the indirect effect (i.e., the effect of the intervention (IE or IR) on treatment outcome through a specific mediator). For these analyses, we will use bootstrapping [72, 73], a nonparametrical procedure that produces an estimate of the sample distribution based on several resamples. For the proposed analyses, a minimum of *n* = 5000 bootstrap resamples will be generated. To the best of our knowledge, bootstrap mediation is currently not available for mixed regression. Unless such a technique is available by the time of the analyses, we will execute the bootstrap mediation test on the subsample with complete data, as well as on the complete sample with missing values imputed, to check for consistency of results. A multiple imputation procedure based on 20 datasets will be used to replace missing values.

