The proposed study also has a number of weaknesses. First, consistent mediator assessment might be compromised by the logistical complexity of the study. More specifically, while we aim at assessing treatment outcome variables and mediators every 7 days, appointments might sometimes be cancelled and/or rescheduled. In order to maintain the temporal relationship between mediators and outcome variable measurements as stable as possible, appointments may only be (re)scheduled to a *later* time point. Second, due to practical considerations, the proposed study has a relatively small sample size. Therefore, its statistical power might be too small to detect statistically significant differences between IE and IR with regard to treatment efficacy and/or mediators of change. However, exploring potential differences between IE and IR might inspire future research in this domain. Third, the waiting-list period of the proposed study is rather short. As a consequence, we cannot assess the long-term effects of the stripped-down treatments. However, if the results of the proposed trial support the efficacy of both interventions, future research might directly compare the two techniques as described in the present treatment protocol to a waiting-list condition with a longer waiting period. Fourth, two of the questionnaires used in the present study have not yet been validated (NDIQ and NBQ). It should be noted that the outcome variables used in nightmare treatment studies often lack precise definitions. With regard to nightmare research, it has become customary to assess nightmare frequency and nightmare distress. Such nightmare distress can be measured either in terms of distress directly associated with nightmares (e.g., NDQ [57]), or in terms of the effects nightmares have on a person’s life (e.g., NES [58]). While these questionnaires tap into different constructs of nightmare distress, they also show some considerable overlap. Therefore, we decided to create a nightmare distress outcome measure (i.e., NDIQ), which combines different aspects of nightmare distress in a single questionnaire. We acknowledge that a lack of validation might reduce confidence in the NDIQ as an outcome measure. However, the NDIQ is constructed from items resembling those of two validated questionnaires (NDQ and NES). Given that the items included in the NDIQ are very similar to those from these other questionnaires, we expect the NDIQ to be a valid and reliable measure. As to the NBQ, it should be mentioned that dysfunctional nightmare beliefs have not systematically been studied to date. The NBQ, a novel questionnaire altogether, aims to assess the occurrence of dysfunctional nightmare beliefs in nightmare sufferers. It was constructed to resemble other validated dysfunctional beliefs questionnaires (e.g., Dysfunctional Beliefs and Attitudes about Sleep [74]; Panic Belief Inventory [75]; Metacognitions Questionnaire [76]). To assess the psychometric properties of the NDIQ and NBQ, prior to data analyses, both questionnaires will be validated within a representative sample of nightmare sufferers and healthy controls. Fifth, the selected mediators are assumed to play a crucial role in IE, IR, or both. While we acknowledge that there are a multitude of (other) proposed theories and processes underlying IE and IR, we focus on those variables that have recently received much attention in the empirical literature and that seem especially relevant in the treatment of nightmares. Accordingly, it is possible that other relevant processes or variables were disregarded.

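### At a 7-day gap the sleep-quality mediator rates one of the seven nights the next nightmare count covers, which biases the step-2 screen toward selecting it

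*Protocol article*

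**What the plan says.** The first primary outcome is the NFQ count: "the total number of nightmares in the last week constitutes the first primary outcome measure" (Primary outcome measures). The number of nights with nightmares over the same week is a secondary outcome. Both are collected weekly: "In the beginning of each treatment session, participants will be asked to fill out the primary treatment outcome measures" (Procedure).

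The mediators "are assessed 1 day after each treatment session (and after pre- and post-assessment") (Mediators of change). Table 2 words the sleep-quality item as "How would you evaluate the quality of last night’s sleep". The other six scales in that questionnaire concern nightmares, or the emotions they elicit, in general.

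On spacing, the Discussion says "we aim at assessing treatment outcome variables and mediators every 7 days", while Mediators of change says "the weekly appointments and assessments will be separated by a minimum of 7 and a maximum of 14 days".

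Step 2 of the Mediation section uses each mediator score to predict the outcome "at the following assessment (i.e., 6 days/nights later"), regardless of condition. Only mediators that pass go into the step-3 model and on to step 4. The Discussion lists among the study's strengths that this timing allows temporal and causal relationships to be established.

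**The concern.** The plan relies on each mediator being measured before the outcome it predicts. For sleep quality and the NFQ this fails by one night: the lag is six nights but the outcome looks back seven. The seventh is the very night the mediator rates.

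The protocol's own description of nightmares, as dreams that usually wake the sleeper and accompany disrupted sleep, gives the likely direction. A nightmare on the shared night lowers the rating and adds to the count. An association then appears even if sleep quality has no effect on any later nightmare. Adjusting for the previous NFQ does not remove it, because the shared night falls after that count closed.

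At stake is whether sleep quality passes the screen for the NFQ outcomes, and whether the claim of temporal order holds for this pair.

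**Working it through.** **The plan's own figure.** A session on day 0, a questionnaire on day 1 and the next session on day 7 give a lag of 7 − 1 = 6 nights. This reproduces the stated lag.

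**Night count.** Let the questionnaire be answered on day k and the next NFQ on day G. The rated night runs from day k − 1 to day k. The NFQ, taking the last week as seven nights, covers day G − 7 to day G. The rated night is counted if k − 1 ≥ G − 7, that is, if G ≤ k + 6.

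- k = 1, G = 7: night 0–1 is rated and nights 0–1 to 6–7 are counted. One night of seven is shared.
- k = 1, G = 8 to 14: the count starts at night 1–2 or later. Nothing is shared.
- k = 2, G = 8: night 1–2 is rated and is the first one counted. One night is shared, so late answering matters.

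**Induced correlation.** Let r be the correlation between the rating and that same night's nightmares (assumed; not in the documents). With independent nights of equal variance, the covariance with the weekly count comes only from the shared night and the count has seven times the nightly variance, so the correlation with the count is r/√7.

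**Step 2, set-up A.** Sleep quality has no effect. There are 90 participants with four lagged pairs each (T1→T2 to T4→T5). Assumed: nightmare probability 0.4 per night, residual SD 20, all gaps 7 days, equal propensity. Analysis: Poisson GEE adjusted for the previous NFQ, 400 trials per setting.

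| Drop in rating after a nightmare | Selected, seven nights | Selected, shared night removed |
|---|---|---|
| 10 points | 40% | 4% |
| 20 points | 92% | 6% |
| 30 points | 100% | 6% |

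A repeat run gave about 47%, 88% and 100% with the overlap.

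**Step 2, set-up B.** Poisson nightmares at 2 or 4 per week, within-person correlation test, four lags, same null.

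| r | r/√7 | Selected, 90 participants | Selected, 60 treated |
|---|---|---|---|
| −0.3 | −0.113 | 45–47% | 32–36% |
| −0.5 | −0.189 | 86–88% | 72–73% |
| −0.7 | −0.265 | 99% | 94–95% |

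Counting only the six later nights gave 4–6%.

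**Relaxing the assumptions.**

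- Only 60% of gaps at 7 days (assumed), set-up A: about 14%, 49% and 75% for 10, 20 and 30 points.
- Propensity varying between people (logit SD 0.8 to 1.2, assumed): the six-night outcome still rejected in about 9–43% of null trials.
- Pooled rather than within-person analysis in set-up B (r = −0.5, 60 participants, log-rate SD 0.6): mean correlation −0.30 with the overlap and −0.18 without.

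**Step 4.** Approximated by baseline-adjusted regression, 30 against 30, r from −0.3 to −0.7, with treatment cutting nightmares by 50–65% (assumed) and a Monte Carlo interval in place of the bootstrap. The later mediator rating is the one that shares a night with the post-assessment count.

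| Quantity | Overlap | Shared night removed |
|---|---|---|
| Mean indirect effect (nightmares/week) | −0.02 to −0.23 | about 0 to −0.08 |
| Mediator-to-outcome slope significant | 11–61% | 5–16% |
| 95% interval excludes 0 | 1–17% | 0.1–5% |

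**The case against.** A reader might infer that the overlap manufactures a false mediator. The documents do not support that. Step 2 is a screen. Mediation is judged at step 4 from the confidence interval of the indirect effect, and with 30 per arm that interval excluded zero in at most 17% of the null trials. The plan also does not say which assessments form the step-4 difference score. If the later rating is the one taken a day after post-assessment, it falls outside the post-assessment window and shares no night with it. What stands is a biased screen, with some bias carried into step 4 if the rating after the third session is used.

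A reader might also take 40% to 100% as the expected error rate. It is conditional on every gap being 7 days, on values the documents do not give, and on all 90 participants entering step 2, although the text ties the scores to treatment sessions. Gaps of up to 14 days are allowed and rescheduling is expected. Still, 7 days is the stated aim and the basis of the 6-night lag.

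Nor does removing the shared night bring the error rate back to 5%. That held only with equal propensity or a within-person test. Stable differences between people leave an association of their own.

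The reach is narrow. Sleep quality is one of eight mediators, is not hypothesised as specific to either treatment, and the argument does not extend to the nightmare distress score (NDIQ). Recruitment was in its final stage, so a new item can help few participants, if any. All of this limits the importance of the point without removing it.

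**Conclusion.** The overlap follows from the stated schedule: at a 7-day gap with day-1 answering, one of the seven nights in the NFQ window is the night the mediator rates, and the Mediation section does not exclude it. This biases step 2 toward selecting sleep quality for the number of nightmares and the number of nights with nightmares, and undercuts the claim of temporal order for this pair.

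Under the assumptions in set-up A, a sleep-quality variable with no effect passes the screen in roughly 40–100% of trials. The rate is lower when some gaps are 8 to 14 days or only treated participants enter. A false final result at step 4 is much less likely, about 1–17%. Direction and size both rest on a nightmare lowering that night's rating, which is plausible but not quantified in the documents.

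The sample size, the efficacy comparisons and the NDIQ analyses are unaffected. This is a cheap improvement to the mediation analysis and does not threaten the trial's main conclusions.

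**What to change.** **Data collected without a last-night nightmare count.**

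- Do not select or interpret last-night sleep quality as a mediator of the NFQ outcomes from 7-day gaps.
- Either restrict that lagged model to intervals of 8 days or more, as a sensitivity analysis, or report the association as partly concurrent. Check the restriction against the date the questionnaire was answered: the next NFQ must be at least 7 days after it.
- Keep sleep quality as a candidate mediator for the NDIQ.
- Qualify the Discussion's claim of temporal and causal order for sleep quality and nightmare frequency.

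**Assessments still to come.** Add one item to the T + 1 day questionnaire: the number of nightmares last night. At 7-day gaps, subtract it from the next NFQ count and model the other six nights with offset log 6. For nights with nightmares, drop the shared night in the same way.

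The weekly sleep-quality scale under Other measures is not a ready substitute. It is conditional ("If participants experienced one or more nightmares during the previous week, they will be asked to fill out four questions about the impact"), so it is missing for those free of nightmares that week. Completed at a session, it also describes nights before that session and cannot carry that session's effect.

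**Cost.** Some analysis wording and, where still possible, one online item. The loss is reduced information on one exploratory mediator for one primary outcome and its secondary companion. Longer intervals arise through rescheduling, so that subset may be small and unrepresentative. Neither step removes confounding by stable between-person differences, so a return to the nominal 5% should not be claimed.
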